## Abstract

**Background:**

This randomized Phase III trial will evaluate whether the methylene blue-assisted technique is efficient for harvesting lymph nodes after radical surgery for gastric cancer.

**Methods/design:**

Patients that undergo distal or total gastrectomy with radical nodal dissection will be randomly assigned to Group A: the standard group, the lymph nodes (LNs) will be harvested from the fresh specimen immediately after surgery, or Group B: the methylene blue-assisted group, where the LNs will be harvested from specimens fixed with 10% buffered formalin with methylene blue for 48 hours after surgery. The primary endpoint is the ratio of the number of the harvested LNs per time (minute). The secondary endpoint is the number of harvested LNs. A 25% reduction in the ratio of harvested lymph-node/time (minute) was determined to be necessary for this test treatment, considering the balance between the cost and benefit. Retrospective data was used to estimate the ratio of the number of the harvested LNs per time (minute) to be 40/30 minutes in Group A. A 25% risk reduction and a rate of 40/22.5 minutes is expected in Group B. Therefore, the sample size required ensuring a two-sided alpha error of 5% and statistical power of 80% is 52 patients, with 26 patients per arm. The number of patients to be accrued was set at 60 in total, due to the likelihood of enrolling ineligible patients.

**Trial registration:**

UMIN000008624

## Background

Gastric cancer is the second most frequent cancer-related cause of death after lung cancer [1]. Surgical resection with radical lymphadenectomy is a standard treatment when gastric cancer is a local disease. Treatment strategy is determined based on the pathological diagnoses of tumor invasion and lymph-node metastasis. When determining N factor, TNM classification recommends nodal examination at least 16 or more regional lymph nodes (LNs) [2].

Nodal sampling from the specimens could be affected by physician’s experience, extent of dissection, type of gastrectomy, and the method for harvesting LNs. Surgeons harvest LNs from the fresh specimens immediately after surgery in Japan, while the pathologists from the specimens fixed with formalin after surgery in other countries [3]. Although surgeons may be more enthusiastic for harvesting LNs than pathologists, it must be tough to do such work just after surgery. On the other hand, nodal sampling may be difficult for pathologists who are not familiar with surgical anatomy. Moreover, the tissues fixed by formalin are hard and difficult to be separated; by which nodal sampling must be time-consuming work for most pathologists.

Methylene blue-assisted technique is another approach for harvesting LNs. The specimens are fixed with formalin with methylene blue after surgery, by which physicians are easy to pick up LNs stained by blue dye. Recently, a pathologist, Märkl reported in colon cancer that the methylene blue-assisted technique was significantly superior than the conventional methods in the number of and the time for harvesting LNs when the samples were fixed with formalin [4]. In gastric cancer, a few Japanese surgeons reported efficacy of this method in single arm studies [5,6]. It remains unclear whether the methylene blue-assisted technique is superior to standard method using the fresh samples.

Based on these, we conducted a randomized phase III study to confirm the superiority of the methylene blue-assisted technique compared with the standard approach using the fresh sample in harvesting LNs by surgeons after gastrectomy with radical lymphadenectomy for gastric cancer.

## Methods/design

### Purpose

The purpose of the study is to confirm the efficiency of the methylene blue-assisted technique in comparison to the standard approach using fresh samples for harvesting LNs by surgeons after gastrectomy with radical lymphadenectomy for gastric cancer.

### Study setting and protocol review

The study is an open-label, randomized Phase III trial. The protocol has been approved by the Institutional Review Committee of Kanagawa Cancer Center.

### Endpoints

The primary endpoint is the ratio of the number of the harvested LNs per time (minute). The secondary endpoint is the number of harvested LNs. We set the ratio of the number of the harvested LNs per time (minute) as the primary endpoint because this is a measure for the efficacy; however, the stage migration is a measure for the accuracy not for the efficacy. Theoretically, the test arm has a superior in the efficacy but the same accuracy as compared with the control arm. To guarantee this, we set the stage migration as a secondary endpoint.

### Eligibility criteria

The tumors will be staged according to Japanese classification of gastric carcinoma 3rd English edition [7]. The inclusion criteria are:

(i). Histologically proven adenocarcinoma of the stomach.

(ii). Clinical stage 1–3 disease.

(iii). R0 resection is achieved by gastrectomy with D1+ or D2 lymphadenectomy according to Japanese gastric cancer treatment guidelines 2010 (ver. 3) as a primary treatment [8].

The patients that receive any other treatment before surgery will be excluded.

All participants gave written informed consent before study entry.

### Registration

Surgeons will register the eligibility criteria to the data center after confirmation during the surgery. The patients will be randomized and assigned to the standard group and the methylene blue-assisted group by a centralized dynamic method using the following factors: lymphadenectomy (D1+/D2), type of gastrectomy (subtotal/total), and surgical experience (less than 15 years/15 years-). The accrual was started in August 2012 and is to continue for 1 year.

#### Qualification of the participating surgeons

All surgeons have previous experience in harvesting LNs from more than 50 specimens.

### Statistical methods

The present study is a randomized phase III study to evaluate the efficiency of the methylene blue-assisted lymph node technique for harvesting LNs after surgery for gastric cancer. The primary endpoint is the ratio of the number of the harvested LNs per time (minute). A 25% reduction in the ratio of harvested lymph-node/time (minute) is necessary for this test treatment, considering the balance between the cost and benefit. Retrospective data from this institution was used to estimate the ratio of the number of the harvested LNs per time (minute) to be 40/30 minutes in the control arm. A 25% risk reduction in the test arm is expected, with a rate of 40/22.5 minutes in the test arm. This situation, will require a sample size of 52 patients, with 26 patients per arm to ensure a two-sided alpha error of 5% and statistical power of 80%. A total of 60 patients will be accrued due to the likelihood of enrolling ineligible patients.

The primary end point of the study is analyzed in the intent-to-treat (ITT) population using a Wilcoxon rank-sum test. The secondary endpoints, number of harvest lymph node and time of harvested lymph nodes are similarly analyzed using a Wilcoxon rank-sum test. Multivariate analysis is also used to analyze those endpoints with adjustment for clinically important background factors.

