## Discussion

According to the results of the JCOG9501 trial, which was a Japanese multicenter phase III study to compare D2 and D2 plus para-aortic dissection for gastric cancer surgery, the median number of harvested LNs was 54 (range: 14–161) in the D2 group and 74 (range: 30–235) in the extended para-aortic dissection group [9]. In this trial, the experienced surgeons harvested LNs from the fresh specimens immediately after surgery. These data suggested that the number of harvested LNs tended to be much higher for extended dissection than normal D2, but that there was a wide variation even in D2 dissection. The first possible reason for this wide variation is that the number of LNs is different in each patient. However, no literature supports this possibility. The second possible reason is the difference in the gastrectomy type. The extent of nodal dissection was limited in the distal D2 gastrectomy compared with total D2 gastrectomy. The third possible difference is the skill of the surgeon for harvesting the LNs. In the present trial, we set the type of gastrectomy, extent of lymph node dissection, and surgeon’s experience as the stratification factors. Therefore, we will be able to minimize these effects regarding the differences in the standard method and methylene blue-assisted technique.

The hypothesis of the present study is that the methylene blue-assisted technique is superior to the conventional method, and is associated with a 25% reduction in the ratio of harvested lymph nodes/time (minutes). In general, the statistical hypothesis is determined by considering the balance between the risks and benefits of the standard arm and the test arm. However, there is no risk associated with the methylene blue-assisted technique for the patients. Therefore, it is possible to conclude that the methylene blue-assisted technique is effective even when the difference in the ratio of harvested lymph nodes/time is very small. However, it is not practical to statistically prove the significance of small differences. Considering the practical and acceptable sample sizes based on the previous data, we determined our statistical hypothesis.

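### The primary Wilcoxon test ignores the three allocation factors; it stays valid, but it is conservative and forgoes power if those factors predict nodes per minute

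*Protocol article*

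**What the plan says.** All references are to the protocol article.

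- **Registration:** patients are allocated "by a centralized dynamic method using the following factors: lymphadenectomy (D1+/D2), type of gastrectomy (subtotal/total), and surgical experience (less than 15 years/15 years" or more). These are three two-level factors.
- **Discussion:** "we set the type of gastrectomy, extent of lymph node dissection, and surgeon’s experience as the stratification factors", followed by the expected benefit: "Therefore, we will be able to minimize these effects regarding the differences in the standard method and methylene blue-assisted technique".
- **Statistical methods, primary analysis:** "The primary end point of the study is analyzed in the intent-to-treat (ITT) population using a Wilcoxon rank-sum test". No stratum or covariate is attached to this test. Node count and harvest time are tested in the same way.
- **Statistical methods, further analysis:** "Multivariate analysis is also used to analyze those endpoints with adjustment for clinically important background factors". This comes in addition to the Wilcoxon test.
- **Statistical methods, size:** 26 patients per arm for two-sided 5% error and 80% power, with 60 to be accrued.

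**The concern.** Dynamic allocation makes the arms more alike on the three factors than simple randomisation would. The rank-sum test takes its reference variance from simple randomisation, so it still allows for chance imbalance that the allocation has largely removed. If the factors are prognostic, the test statistic varies less under the null than the test assumes, and the true error falls below 5%. The spread due to the factors also stays in the comparison as noise.

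The Discussion's aim is therefore only half met: balancing deals with imbalance between the arms but does not remove the factors' contribution to the residual spread. The planned multivariate analysis does not recover this, because the unadjusted Wilcoxon is the test named for the primary endpoint. At stake is precision in a small trial.

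**Working it through.** **Inputs from the protocol article.** Two-sided error 5%, power 80%, 26 per arm. Control rate "to be 40/30 minutes in the control arm", that is 40/30 = 1.333 nodes per minute. Test-arm rate 40/22.5 = 1.778. Difference 0.444. Accrual 60. Three two-level factors give 2 × 2 × 2 = 8 combinations, so 52/8 = 6.5 patients per combination on average.

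**Assumptions (not in the documents).** R², the share of outcome variance explained by the three factors together, is varied from 0 to 0.5 and divided equally among them. Factor prevalences are 0.6, 0.3 and 0.5. Allocation is minimisation on marginal totals with a biased coin of 0.8. The outcome is normal with a constant treatment shift.

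**Step 1: the planned effect.** No standard deviation is given, so the 52 cannot be reproduced directly. Solving backwards from 26 per arm:

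SD = 0.444 × √(26/2) / (1.960 + 0.842) = 0.444 × 3.606 / 2.802 = 0.572 nodes per minute

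The standardised difference is 0.444/0.572 = 0.777. The simulations use this value.

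**Step 2: direction of the effect on the error rate.** If balance on the factors were perfect, the null variance of the treatment comparison would shrink by roughly (1 − R²). The nominal cut-off of 1.96 would then act as 1.96/√(1 − R²):

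- R² = 0.1: 1.96/√0.9 = 2.07, two-sided error about 3.9%
- R² = 0.2: 1.96/√0.8 = 2.19, about 2.8%
- R² = 0.3: 1.96/√0.7 = 2.34, about 1.9%

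Real minimisation balances imperfectly, so the true figures should usually lie between these and 5%.

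**Step 3: simulation with 52 patients** (4,000 trials per setting; simulation error about 0.3 points on the error rate and 0.7 points on power). The adjusted analysis regresses the ranks on treatment and the three factors as main effects.

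| R² | Error, Wilcoxon | Error, adjusted ranks | Power, Wilcoxon | Power, adjusted ranks | Power, 8-cell stratified Wilcoxon |
|---|---|---|---|---|---|
| 0 | 4.3% | 4.4% | 77% | 77% | 67% |
| 0.1 | 4.1% | 4.9% | 77% | 79% | 72% |
| 0.2 | 3.1% | 5.2% | 80% | 86% | 78% |
| 0.3 | 2.3% | 5.0% | 77% | 88% | 81% |
| 0.5 | 1.4% | 5.6% | 81% | 96% | 93% |

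The power forgone is about 0, 2, 6, 10 and 15 points. A second simulation of the same comparison with 52 patients gave Wilcoxon error rates of 4.4, 3.6, 3.2 and 2.4% at R² = 0, 0.1, 0.2 and 0.3, and power forgone of about 0, 3, 6 and 10 points. The two agree within simulation error.

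The 77% at R² = 0 is not caused by ignoring the factors, since both rank analyses show it. The effect was calibrated with a formula for means, and rank tests are slightly less efficient for normal data (factor 0.955).

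**Step 4: at the accrual target of 60.** Over R² = 0, 0.1, 0.2, 0.3 and 0.5, Wilcoxon power is 82, 83, 84, 86 and 88%. Adjusted rank power is 82, 85, 90, 93 and 98%.

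**Step 5: full stratification.** The last column shows why stratifying by all eight combinations is not a safe remedy. With about 6.5 patients per combination it costs 10 points at R² = 0 (67 v 77%) and 5 points at R² = 0.1 (72 v 77%).

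**The case against.** The strongest reply is that the plan delivers what it promises. The Wilcoxon error does not exceed 5% beyond simulation error. Its power is 77 to 81% with 52 patients and 82 to 88% with the 60 to be accrued. A reader might infer that the stated 5% is breached or that the trial is underpowered because of this test. Neither follows: what is lost is power beyond the target.

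A reader might also infer from the Discussion that the three factors are known to drive the primary endpoint. The text does not go that far. It discusses the number of nodes, whereas the primary endpoint is nodes per minute. A larger specimen may raise both count and time and partly cancel in the ratio. Gastrectomy type and surgeon skill are offered only as possible reasons. Extent of dissection is not among the numbered reasons, and the only dissection comparison cited is D2 against D2 plus para-aortic dissection, not D1+ against D2. All surgeons must have handled more than 50 specimens, which may narrow differences in skill. An R² of 20% or more is therefore an assumption, and at 10% or less the loss is only 0 to 3 points.

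Finally, an adjusted analysis is already planned. It would be tempting to fault it for listing no covariates and stating no rule for disagreement with the Wilcoxon. That is detail commonly left to the analysis plan, and the natural reading is that the Wilcoxon decides. That same reading is why the adjusted analysis does not answer the point.

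What stands against all this is an asymmetry: main-effects adjustment costs nothing in these simulations when the factors are unrelated to the outcome, and it gains power when they are related.

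**Conclusion.** The point holds as a matter of efficiency, not validity. The named primary test leaves out the three factors used in allocation. If they explain 0, 10, 20 or 30% of the variance in nodes per minute, the true error with 52 patients is about 4.4, 3.6, 3.2 and 2.4%, and the power forgone is about 0, 3, 6 and 10 points. The direction follows from balancing on prognostic factors and then testing without them. The size depends on an R² that the documents do not give, and on the assumed minimisation scheme, factor prevalences and normal outcome. The documents do not support calling the planned test invalid or the planned power lost.

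**What to change.** Make the primary analysis a rank ANCOVA: regress the ranks of nodes per minute on treatment group, extent of lymphadenectomy, type of gastrectomy and surgical experience, as main effects and with the levels used at registration, and test treatment at two-sided 5%. Do not replace the test with a Wilcoxon stratified by all eight combinations. Keep the unadjusted Wilcoxon as a sensitivity analysis, and use the same adjusted analysis for node count and harvest time.

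The cost is a change of wording in the protocol's statistical section. Because the primary test is fixed there and the trial is open-label, the change should be made and documented before the data are analysed. No new data are needed, since the three factors are already recorded at registration, and the sample size can stay as it is.

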## Discussion

According to the results of the JCOG9501 trial, which was a Japanese multicenter phase III study to compare D2 and D2 plus para-aortic dissection for gastric cancer surgery, the median number of harvested LNs was 54 (range: 14–161) in the D2 group and 74 (range: 30–235) in the extended para-aortic dissection group [9]. In this trial, the experienced surgeons harvested LNs from the fresh specimens immediately after surgery. These data suggested that the number of harvested LNs tended to be much higher for extended dissection than normal D2, but that there was a wide variation even in D2 dissection. The first possible reason for this wide variation is that the number of LNs is different in each patient. However, no literature supports this possibility. The second possible reason is the difference in the gastrectomy type. The extent of nodal dissection was limited in the distal D2 gastrectomy compared with total D2 gastrectomy. The third possible difference is the skill of the surgeon for harvesting the LNs. In the present trial, we set the type of gastrectomy, extent of lymph node dissection, and surgeon’s experience as the stratification factors. Therefore, we will be able to minimize these effects regarding the differences in the standard method and methylene blue-assisted technique.

The hypothesis of the present study is that the methylene blue-assisted technique is superior to the conventional method, and is associated with a 25% reduction in the ratio of harvested lymph nodes/time (minutes). In general, the statistical hypothesis is determined by considering the balance between the risks and benefits of the standard arm and the test arm. However, there is no risk associated with the methylene blue-assisted technique for the patients. Therefore, it is possible to conclude that the methylene blue-assisted technique is effective even when the difference in the ratio of harvested lymph nodes/time is very small. However, it is not practical to statistically prove the significance of small differences. Considering the practical and acceptable sample sizes based on the previous data, we determined our statistical hypothesis.

In this trial, the primary endpoint is the ratio of the number of harvested LNs per time period (minutes). Our goal is to evaluate the efficacy of harvesting LNs by surgeons. On the other hand, the difference in the number of harvested LNs could produce stage migration between the two groups even though the number of nodal examinations was more than 16 in each group. Therefore, an expletory analysis is needed to evaluate the stage migration and cancer survival in the two groups.
